### Data analysis

Once randomized, each patient will be analyzed in the group to which they were assigned, independent of potential drop-out or compliance to the protocol, according to the intention-to-treat principle. Potential baseline differences between the groups will be tested using independent *t* tests for continuous variables, the Mann-Whitney *U* test for ordinal variables, and chi-square tests for categorical variables.

Outcomes of the measures over time will be compared for the experimental condition versus the control condition using repeated measurements analysis. This analysis takes into account the correlation of repeated measurements within the same patients and it can handle missing data, assuming that data are missing at random. The dependent variable is the outcome measure and the independent variables are time and group assignment and the interaction between these variables. In these analyses, adjustments can be made for potentially confounding variables that could be unequally distributed over the groups despite the randomization procedure.

To evaluate cost-effectiveness, direct (para)medical costs and the total costs of all separate treatments by health care providers during the intervention period will be summed, as well as the costs of the facilities and materials used for these treatments. In addition, the non-medical costs, such as productivity loss, will be calculated. The incremental cost-effectiveness ratio will be calculated by dividing the difference in total costs by the difference in Quality-adjusted Life Years (QALYs), based on the EQ-5D. A net health-benefit analysis will be used to relate the costs to the benefit. We assume that the economic value of 1 life year in good health amounts to 25,000–50,000 €. The economic evaluation will be performed following the Dutch guidelines [53].

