### Measurement instruments

Table 2 gives an overview of the measurement instruments being used. The primary outcome measure is the score on the Boston Naming Test (BNT) [40], to assess picture-naming. Secondary outcome measures are chosen to evaluate generalization of treatment effects to verbal communication: the Aphasia Severity Rating Scale (ASRS) [41] to assess spontaneous speech and the Amsterdam Nijmegen Everyday Language Test (ANELT) [42] as a measure for verbal communication in everyday life. Other secondary outcome measures are chosen to evaluate quality of life (EuroQol-5D, [43]; Stroke and Aphasia Quality Of Life questionnaire (SAQOL), [44, 45]), social participation (Community Integration Questionnaire, [46]), and cost-effectiveness (Cost Analysis Questionnaire, [47–49]).

**Table 2 Tab2:** Measurement instruments

Language and communication tests
Boston Naming Test (BNT) [40]
Aphasia Severity Rating Scale (ASRS) [41]
Amsterdam Nijmegen Everyday Language Test (ANELT) [42]
Shortened Token Test [50]
Quality of life questionnaires
EuroQol-5D (EQ-5D) [43]
Stroke and Aphasia Quality Of Life questionnaire (SAQOL) [44, 45]
Other tests
Community Integration Questionnaire (CIQ) [46]
Cost Analysis Questionnaire [47–49]
Barthel Index [51]
Edinburgh Handedness Inventory
Wong-Baker Faces pain rating scale [52]

The primary outcome measure, BNT, is assessed before and after each intervention week (T1, T2, T3, T4) and at 6 months’ follow-up (T5); see Fig. 2. The secondary outcome measures are assessed before the first intervention week and after the second intervention week (T1, T4) and at 6 months (T5). The EuroQol-5D (EQ-5D) and the Cost Analysis Questionnaire are used to evaluate cost-effectiveness during the 4-week intervention period and during the follow-up period.

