### Sample size

The power calculation is based on the results of a randomized controlled trial by Baker et al. [11] including stroke patients in the chronic phase. In this study the group of aphasia patients trained with tDCS improved 2.1 points more than a sham-control group on a picture-naming test. Cohen’s *d* effect size was 0.22, which is equal to a Cohen’s *f* of 0.11. For the present study we calculated that, using a study design with two groups and four repeated measurements, a within-patient correlation of 0.75, an alpha of 0.05, a power of 0.80 and a Cohen’s *f* effect size of 0.11, we need a total group of 58 patients (29 patients in each treatment arm).

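### No decisive term or visit is named, and N = 58 matches an unsigned 3-df interaction test; a signed, baseline-adjusted T4 contrast should be primary and N = 58 restated for it

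*Protocol article*

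**What the plan says.** - **Analysis (Data analysis).** One repeated-measures model is described for all outcomes: "the independent variables are time and group assignment and the interaction between these variables". The section does not say which term decides the trial, whether time is categorical, which visits enter, or which visit is primary.
- **Visits (Measurement instruments).** The BNT, the primary outcome, "is assessed before and after each intervention week (T1, T2, T3, T4") and again at 6 months (T5), so five times.
- **Sample size.** The calculation assumes "two groups and four repeated measurements", a within-patient correlation of 0.75, "an alpha of 0.05", "a power of 0.80" and f = 0.11, giving 58 patients (29 per arm). The f comes from d = 0.22 in an earlier trial in chronic patients, whose tDCS group "improved 2.1 points more than a sham-control group on a picture-naming test".
- **Hypothesis (Discussion).** The stated expectation has a direction: tDCS should speed up language recovery.

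**The concern.** The hypothesis has a direction, but the only between-arm comparison described is a profile model, and the sample size fits a multi-df test of parallel profiles. A test of that kind rejects for any departure from parallelism: tDCS ahead, sham ahead, a transient difference, or a divergence that arises only in the pause between T2 and T3. A significant F would not settle whether naming was better after treatment, and the F statistic gives no single effect estimate. Because the decisive term and visits are open, two analysts could choose T1 to T4 or T1 to T5, or the interaction or one visit, and reach different conclusions from the same data.

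**Working it through.** **1. Reproducing N = 58.** Inputs from Sample size: f = 0.11, m = 4 visits, correlation ρ = 0.75, α = 0.05, two groups. For the time-by-group interaction (noncentral F, sphericity assumed):

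λ = N·m·f²/(1 − ρ), df1 = m − 1, df2 = (N − 2)(m − 1).

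- N = 58: λ = 58 × 4 × 0.0121/0.25 = 11.23, df = 3 and 168, power 0.803.
- N = 56: λ = 10.84, power 0.787. The smallest even N is 58, as stated.
- Group main effect, λ = N·m·f²/(1 + (m − 1)ρ) = 58 × 4 × 0.0121/3.25 = 0.864: power 0.150, and N = 530 would be needed.
- Interaction over five visits with f still 0.11: df1 = 4, power 0.859 at N = 58, and N = 52 for 80%.

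Of these readings, only the 3-df interaction over four visits returns 58.

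**2. What that test reacts to.** Let D be the between-arm difference in single-visit SD units, with a profile over T1 to T4. Then f is half the SD of the differences across visits. D = 0.5 is an assumption made for this review. The comparators are a two-sided t test at T4 with 29 per arm:

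- baseline-adjusted: SD factor √(1 − ρ²) = √0.4375 = 0.661, noncentrality 0.5/(0.661 × √(2/29)) = 2.88, 55 df, power 0.807;
- change from T1: SD factor √(2(1 − ρ)) = 0.707, power 0.754;
- T4 difference without baseline: SD factor 1, power 0.465.

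| Profile (T1, T2, T3, T4) | 3-df omnibus | Baseline-adjusted T4 |
|---|---|---|
| Gain in each intervention week (0, D/2, D/2, D) | 0.595 | 0.807 |
| Linear (0, D/3, 2D/3, D) | 0.646 | 0.807 |
| Single step (0, D, D, D) | 0.789 | 0.807 |
| Sham ahead (0, −D, −D, −D) | 0.789 | 0.807, with the sign shown |
| T3 only (0, 0, D, 0) | 0.789 | no T4 difference to detect |
| Divergence in the pause (0, 0, D, D) | 0.900 | 0.807 |
| Lead lost in the pause and regained (0, D, 0, D) | 0.900 | 0.807 |
| Early lead that narrows (0, D, D/2, D/2) | 0.595 | 0.293 |

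Adding T5 to the first profile, with the T4 difference either kept or gone at T5, gives a 4-df test with power 0.713.

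**3. What N = 58 delivers for a T4 contrast.** By the normal approximation, the difference detectable with 80% power is (1.960 + 0.842) × SD factor × √(2/29):

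- baseline-adjusted: 2.802 × 0.661 × 0.2626 = 0.49 SD;
- change from T1: 2.802 × 0.707 × 0.2626 = 0.52 SD.

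Suppose 0.22 is a T4 difference in single-visit SD units (an assumption; the article gives no SD). Power at 29 per arm is then 0.238 baseline-adjusted and 0.214 for change. Reaching 80% would take 142 per arm (284) or 163 per arm (326).

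The 3-df test does no better on that reading: 0.143 (gain in each week), 0.155 (linear) and 0.197 (step). Its nominal 80% requires the differences to have an SD of 0.22 across visits, which means a T4 difference of 0.62, 0.59 or 0.51 respectively.

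**The case against.** Four arguments deserve an answer.

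**The omnibus test is inferred.** A reader might infer that the protocol declares a multi-df interaction over five visits to be its primary test. It does not. Data analysis lists model terms for every outcome, calls none of them primary, does not say that time is categorical and does not put T5 in a primary model. Nor are four and five visits a contradiction: four fits T1 to T4 with T5 as follow-up, and five visits at the same f would raise nominal power. What stands is that the sample size points to a 3-df interaction and nothing in the article names another deciding test.

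**The analysis plan may settle it.** The model can yield a signed difference at each visit, and the decisive contrast may be specified in a document not shown. So silence alone is not the point. The point is that the stated sample size is tied to a test that does not match the directional hypothesis.

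**The T4 contrast is not always stronger.** It would be wrong to infer that the omnibus test wins only when the effect arises in the pause. It also wins for a lead lost and regained, and for an early lead that narrows. Such patterns are plausible if tDCS mainly speeds recovery, and Study design and procedure values the recovery pattern over time. Unadjusted change from T1 (0.754) is also below the omnibus test for a single step (0.789).

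**T4 is a choice.** The article ranks no visit and stresses a 6-month follow-up. T4 is proposed because it closes the second intervention week.

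**Conclusion.** The point holds in this limited form and is worth acting on. The article fixes no decisive term or visit, and its N = 58 corresponds to an unsigned 3-df interaction that does not by itself show benefit after treatment. The loss of power against a baseline-adjusted T4 contrast is about 21 percentage points if gains occur in each intervention week, 16 if divergence is linear and 2 for a single step. It reverses for some non-monotone or pause-related profiles. The case for change therefore rests first on interpretability and a single prespecified answer, and only second on power. The power figures assume D = 0.5 single-visit SD, equal correlations of 0.75, sphericity and complete data. The 0.81 needs baseline adjustment; without it the T4 difference has 0.465.

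**What to change.** Before unblinding, state that:

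- the primary analysis is the between-group difference in BNT at T4, tested two-sided with 1 df at 0.05;
- it comes from a repeated-measures model on T1 to T4 with categorical time, and baseline BNT is handled as a covariate or through a common T1 mean for both arms;
- the differences at T2, T3 and T5 and the omnibus interaction are secondary.

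Restate what N = 58 delivers for this contrast: about 80% power for a T4 difference of about 0.49 SD, and about 24% (21% for change from T1) if 0.22 is a T4 difference in single-visit SD units. Say which scale 0.22 refers to.

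Cost: wording in the analysis and sample-size sections, with no change to visits or data collection. The price is less sensitivity to effects that have faded by T4 or appear only at T5, and a stated power less favourable than the present 80%.

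### No adjustment for T1 EQ-5D utility is named for the QALY difference in the cost-effectiveness ratio; prespecifying one would sharpen that difference at no data cost

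*Protocol article*

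**What the plan says.** Under Data analysis, the protocol article states that the ICER "will be calculated by dividing the difference in total costs by the difference in Quality-adjusted Life Years (QALYs), based on the EQ-5D". Net health benefit will be analyzed as well, with the assumption: "We assume that the economic value of 1 life year in good health amounts to 25,000–50,000" euro. For methods, the economic evaluation is referred to Dutch guidelines.

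Under Measurement instruments, the EQ-5D is listed among the secondary outcomes, and "The secondary outcome measures are assessed before the first intervention week and after the second intervention week (T1, T4) and at 6 months (T5". The EQ-5D and the cost questionnaire "are used to evaluate cost-effectiveness during the 4-week intervention period and during the follow-up period". A baseline utility will therefore exist for each patient assessed.

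The only statement on covariates stands in the Data analysis paragraph on the repeated-measurements model: "In these analyses, adjustments can be made for potentially confounding variables that could be unequally distributed over the groups despite the randomization procedure". It is permissive, it refers to those analyses, and it is not repeated in the cost-effectiveness paragraph. The same section plans significance tests of baseline differences.

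Under Randomization and blinding, allocation is stratified by center only. Under Sample size, the plan is for 58 patients, 29 per arm.

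**The concern.** A QALY built from T1, T4 and T5 collapses three utilities into one area per patient. A chance difference between arms at T1 enters that area in two ways: directly, through the first segment of the curve, and indirectly, because patients with higher utility at T1 tend to have higher utility at T4 and T5. The clinical outcomes are less exposed, because the time-by-group interaction separates a baseline difference from a difference in change. The QALY loses that separation unless T1 utility is put into the model.

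Stratification by center does not balance utility, and 29 per arm leaves room for chance imbalance. The QALY difference is the denominator of the ICER and feeds the net health benefit. The Discussion makes possible implementation of tDCS depend in part on cost-effectiveness. When the denominator is small, a modest shift can change the size or even the sign of the ratio.

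**Working it through.** **The plan's own figure.** Inputs from Sample size: two groups, four measurements, and "a within-patient correlation of 0.75, an alpha of 0.05, a power of 0.80 and a Cohen’s *f* effect size of 0.11". For the group-by-time interaction, λ = f²·N·m/(1 − ρ) = 0.0121 × 58 × 4 / 0.25 = 11.23, with 3 and (58 − 2) × 3 = 168 degrees of freedom. Power is 0.803, and 58 is the smallest N that reaches 0.80. The planned 29 per arm is therefore reproduced and is used below.

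**Inputs for the QALY.**
- From the article: n = 29 per arm; T1 at week 0; T4 at week 4 (the end of the 4-week intervention period); EUR 25,000-50,000 per QALY.
- Assumed, not in the article: area under the curve by the trapezoid rule from T1; utility SD 0.20-0.30, equal over time; a common correlation ρ of 0.3-0.7 between any two time points; T5 at week 26.

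**Weights.** The trapezoid rule gives T1 2/52, T4 13/52 and T5 11/52, which sum to 26/52 = 0.50 year.

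**Chance imbalance at T1.** SE = SD × √(2/29) = 0.263 × SD, that is 0.053 (SD 0.20) to 0.079 (SD 0.30).

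**Carry-over per unit of T1 utility.** Slope = 2/52 + ρ × 24/52, that is 0.177 at ρ = 0.3, 0.269 at ρ = 0.5 and 0.362 at ρ = 0.7. Divided by the 0.50-year horizon, 35%, 54% and 72% of the imbalance is carried over.

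**Shift in an unadjusted QALY difference from a one-SE imbalance (slope × SE):**

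| SD | ρ | SE at T1 | Slope | Shift (QALY) | EUR at 25,000 | EUR at 50,000 |
|---|---|---|---|---|---|---|
| 0.20 | 0.3 | 0.0525 | 0.1769 | 0.0093 | 232 | 465 |
| 0.25 | 0.5 | 0.0657 | 0.2692 | 0.0177 | 442 | 884 |
| 0.25 | 0.7 | 0.0657 | 0.3615 | 0.0237 | 593 | 1,187 |
| 0.30 | 0.7 | 0.0788 | 0.3615 | 0.0285 | 712 | 1,424 |

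If T5 falls 26 weeks after T4 (week 30), the shares stay at 35-72%, and the shift becomes 0.0105-0.0327 QALY (EUR 263-1,636).

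**What adjustment gains.** The variance of one patient's QALY is SD² × [Σw² + ρ(0.25 − Σw²)], with Σw² = (4 + 169 + 121)/2704 = 0.1087. Adjustment removes SD² × slope². The SE of the difference is the square root of the variance × 2/29. At SD 0.25:
- ρ = 0.3: 0.0255 falls to 0.0227.
- ρ = 0.5: the bracket is 0.1794, less 0.0725; the SE falls from 0.0278 to 0.0215 (40% of the variance removed).
- ρ = 0.7: the bracket is 0.2076, less 0.1307; the SE falls from 0.0299 to 0.0182 (63% removed).

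**The baseline tests do not settle it.** A one-SE imbalance has a test statistic of 1, well short of significance at 0.05. A rule that adjusts only after a significant baseline test would leave every shift in the table in place.

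**The case against.** The strongest reply is that the article does not say the difference is unadjusted. The quoted sentence is the generic definition of an ICER, and a regression-adjusted difference would satisfy it word for word. The article condenses a fuller protocol, and it refers the economic evaluation to guidelines that are not at hand. A reader might infer that the plan has chosen a raw difference; the text does not support that. What stands on the other side is narrower: the cost-effectiveness paragraph names no adjustment, and the one adjustment sentence shown is discretionary and attached to another analysis.

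A reader might also infer that a T1 imbalance passes in full into the QALY difference. It does not. The direct weight of T1 is only 2/52 = 0.038, and total carry-over is about 35-72% at correlations of 0.3-0.7. Full carry-over needs a correlation of 1. Since the Background says recovery is fastest in these first months, the lower correlations are plausible.

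Third, randomization makes the unadjusted difference unbiased on average, and its standard error already includes chance imbalance. That is correct. The harm is lost precision, and bias conditional on an imbalance that is actually observed. Adjustment does not remove the remaining noise either: a standard error of 0.018-0.022 QALY is still worth 0.018 × 25,000 = EUR 450 to 0.022 × 50,000 = EUR 1,100 per patient. That part comes from the sample size.

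**Conclusion.** The point holds as a low-severity improvement. Followed as written, without adjustment, the plan would give a valid ICER denominator that is less precise than its own data allow. The shift from a one-SE imbalance is about 0.009-0.028 QALY, or about EUR 230-1,420 per patient. At SD 0.25 the standard error could fall by roughly a quarter at correlation 0.5 (0.028 to 0.022) and by about two fifths at 0.7 (0.030 to 0.018). These figures depend on the assumed utility SD, correlation, trapezoid area and timing of T5, none of which the article gives. The documents do not support calling the planned estimator biased or invalid, and they do not show that adjustment has been ruled out.

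**What to change.** Add one sentence to the cost-effectiveness paragraph: the QALY difference used in both the ICER and the net health-benefit analysis is estimated by regression of the T1-T5 QALY on arm with T1 EQ-5D utility as a covariate, whatever the baseline significance tests show. Center, as the stratification factor, may be included as well. If the fuller protocol or the cited guidelines already require this, it is enough to say so.

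The cost is one sentence and no new data. By the Trial status section, 44 patients had been included on 2 May 2016 and inclusion was still open, so at that point the rule could be set before the analysis.

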## Discussion

The present study focuses on the effect of tDCS provided during SLT in the sub-acute stage after stroke. The primary aim is to evaluate the potential effect of tDCS on language functioning, specifically on word-finding, as well as generalization effects to verbal communication. The secondary aim is to evaluate its effect on social participation and quality of life, and to evaluate the cost-effectiveness of this intervention.

In line with studies applying tDCS in the chronic stage, we use the most common electrode configuration, i.e., anodal tDCS over the left IFG as compared to sham-tDCS, in combination with disorder-oriented aphasia therapy, aimed at word-finding. The application of tDCS (1 mA for 20 minutes) and the frequency is also chosen in line with studies applying tDCS in the chronic stage. However, the discussion of what may be the optimal electrode configuration and what the optimal stimulation intensity and frequency is, is still ongoing. Regarding the optimal electrode configuration, individual factors such as lesion size and the relative contribution of the RH and the LH and its relation to aphasia recovery, may lead to individual variability in response to tDCS. However, recent fMRI and computer modeling studies find that applying anodal tDCS on the left IFG [30–32] may be a suitable approach.

We expect that tDCS will enhance the speed of language recovery, resulting in improved communication, quality of life and participation – associated with decreased rehabilitation consumption and cost reduction. If we find that tDCS enhances the effect of SLT in an early phase provided that adverse effects are limited at this stage post stroke, and if it is found to be cost-effective, tDCS may be implemented in regular aphasia rehabilitation programs for the sub-acute post-stroke population.

### Trial status

The inclusion of the study started on 17 April 2014 and on 2 May 2016 we had included 44 participants. We expect that the inclusion and the follow-up measurements will be completed in April 2017.

## Abbreviations

ANELT, Amsterdam Nijmegen Everyday Language Test; ASRS, Aphasia Severity Rating Scale; BDNF, brain-derived neurotrophic factor; BNT, Boston Naming Test; CIQ, Communication Integration Questionnaire; EDB, European Data Bank; EQ-5D, EuroQol-5D; IFG, inferior frontal gyrus; LH, left hemisphere; QALYs, Quality-adjusted Life Years; RH, right hemisphere; SAQOL, Stroke and Aphasia Quality Of Life; SLT, Speech and Language Therapy; tDCS, transcranial direct current stimulation.
